### Statistics

2.7

#### Sample size

2.7.1

The sample size was calculated based on the primary outcome. According to a previous related clinical study, the percentage of patients in the EA group, whose CSBMs increased by at least once per week from the baseline, was 69.7% at week 8, while that of the sham EA group was 44.6%.^[19]^ We assume that the corresponding indicator in the present study may be 70% in the EA group and 40% in the TENS group, based on relevant literature reports at home and abroad.^[19–21]^

According to the formula for estimating sample size to evaluate a difference between 2 groups (with 80% power to detect a difference of 30%) in a 2-sided test, each group size should be 42, with an alpha risk of 5% and a beta risk of 20%. Assuming a 20% expulsion rate, a total of 102 participants (51 participants in each group) will be required for the study.

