**Methods::**

Individuals with functional constipation will be randomly allocated to receive either EA or TENS (n = 51, each), 3 times per week for 8 weeks. The primary outcome is the percentage of participants with an average increase from baseline of 1 or more complete spontaneous bowel movements at week 8. The secondary outcome measures are the following: at the time of visits, changes in the number of complete spontaneous bowel movements, number of spontaneous bowel movements, stool character, difficulty in defecation, patients’ assessment of quality of life regarding constipation (self-report questionnaire), and use of auxiliary defecation methods.

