#### Statistical analysis

2.7.2

The statistical analyses will be performed using the SPSS 20.0 statistical software. Continuous data will be represented by the mean, standard deviation, median, minimum value, and maximum value. Categorical data will be represented by percentage. For the data with normal distribution, the *t* test or rank-sum test will be used for continuous data, and a nonparametric test or *χ*^2^ test for categorical data. A rank-sum test or *χ*^2^ test will be used to analyze the difference between 2 independent samples. Statistical analyses will be 2-sided tests. A *P* value <.05 will be considered statistically significant.

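### With 51 per group, a 20% loss leaves about 41, not the 42 that the stated 80% power requires

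*Protocol article*

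**What the plan says.** Section 2.7.1 (Sample size) of the protocol article assumes that the primary responder rate "may be 70% in the EA group and 40% in the TENS group". The test is two-sided, "with an alpha risk of 5% and a beta risk of 20" per cent, and the article concludes that "each group size should be 42". It then adds the allowance for losses: "Assuming a 20% expulsion rate, a total of 102 participants (51 participants in each group) will be required for the study".

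The abstract repeats the group size ("receive either EA or TENS (n = 51, each") and section 2.2 repeats the total of 102, so the figure is not a slip in one place. The article does not show how 42 became 51. It does not define the 20% in any other way, and it does not say that lost participants are replaced or counted as non-responders.

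**The concern.** An allowance for losses should leave the required number evaluable after the losses have occurred. The required number n is therefore divided by (1 − d), where d is the proportion lost. Multiplying by (1 + d) always gives too few, because the loss falls on the enlarged group and not on the original one. Here 51 agrees with multiplication and not with division.

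At stake is whether the total, the loss rate and the power can all be true together. Section 2.7.1 is the only justification given for enrolling 102 participants. If losses reach the planned 20%, the trial falls below its own requirement even when its assumption of 70% versus 40% is exactly right.

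**Working it through.** **Inputs** (section 2.7.1 unless noted): p1 = 0.70, p2 = 0.40, difference 0.30; two-sided alpha 0.05 (z = 1.960); power 0.80 (z = 0.842); 42 per group before losses; loss 20%; 51 per group and 102 in total after the allowance; equal groups (abstract).

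**Step 1: reproduce the 42.** The usual two-proportion formula, with pooled variance under the null hypothesis and no continuity correction, is

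n = [z(α/2)·√(2·p̄·(1 − p̄)) + z(β)·√(p1(1 − p1) + p2(1 − p2))]² / (p1 − p2)², with p̄ = 0.55.

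- √(2 × 0.55 × 0.45) = √0.495 = 0.7036
- √(0.21 + 0.24) = √0.45 = 0.6708
- n = (1.960 × 0.7036 + 0.842 × 0.6708)² / 0.09 = 41.97, rounded up to **42**

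This matches the article, so the base figure is not in dispute.

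**Step 2: find where 51 comes from.**

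| Allowance | Calculation | Per group | Total |
|---|---|---|---|
| n × (1 + d) | 42 × 1.2 = 50.4 | 51 (as stated) | 102 |
| n / (1 − d) | 42 / 0.8 = 52.5 | 53 | 106 |

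**Step 3: apply the planned loss to 51.** 51 × 0.8 = 40.8, that is 40 or 41 per group, against 42 required. The largest loss that still leaves 42 is 1 − 42/51 = 17.6%, or 9 of 51.

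**Step 4: power at the numbers left.** By the same formula, power = Φ[(0.30·√n − 1.960 × 0.7036) / 0.6708].

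| Evaluable per group | Power, planning formula | Power, exact enumeration of the uncorrected chi-square test |
|---|---|---|
| 40 | 78.0% | 79.6% |
| 40.8 | 78.8% | not applicable |
| 41 | 79.0% | 81.3% |
| 42 | 80.0% | 82.8% |

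The exact figures move in steps. With 41 in one group and 40 in the other, exact power is 77.6% or 77.8%, depending on which group is larger.

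**Step 5: the shortfall.** 53 − 51 = 2 per group; 106 − 102 = 4 in total, or 3.9% of 102.

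**The case against.** Four arguments can be made for leaving the figure alone.

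- **The route to 51 is inferred.** The article shows no formula, and if the 20% was meant as a margin added to 42, then 51 is correctly computed. It is fair to say that the multiplication is an inference. But the text speaks of an expulsion rate, and a rate of loss ordinarily applies to those enrolled; nothing in the article defines it otherwise. On that reading the shortfall does not depend on how 51 was reached, since 51 × 0.8 is below 42 either way.
- **The missed power depends on the approximation.** The analysis section names a chi-square test, and its exact power without continuity correction is 81.3% at 41 per group, above 80%. The unpooled planning formula would need only 40 per group (39.2 rounded up). This stands as evidence that the shortfall is small and that 79% is a planning-formula figure. It does not reconcile the stated numbers: exact power is below 80% at 40 per group and at a 41/40 split, and the plan itself set the requirement at 42.
- **Lost participants may stay in the analysis.** The article names no analysis population, and the full protocol or SAP may settle this. It is true that the 79% assumes losses leave the primary analysis. Yet an allowance for losses presupposes the same thing. Counting a 20% loss as non-response would turn 70% and 40% into 56% and 32% (each × 0.8), a 24-point difference, and would lower the power.
- **It is immaterial.** One or two points of power matter less than the assumed 30-point difference; the earlier study cited in the same section found 69.7% versus 44.6%, about 25 points. This is correct as a judgement of consequence. It is a reason to call the error minor, not to leave a wrong figure in place.

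**Conclusion.** The concern holds. The 42, the 20% loss and the 51 per group conflict under the ordinary meaning of a loss rate. The consistent figure is 53 per group, 106 in total. As designed, the trial is 2 per group short at its own planned loss, with power of about 79% by its own formula (78.0% at 40 per group, 79.0% at 41) against the stated 80%.

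This rests on three assumptions: that the 20% is a proportion of those randomised, that lost participants are neither replaced nor kept in the primary analysis, and that the plan's own 42 is the yardstick. The consequence is small and the design is sound in this respect. What needs correcting is the stated justification for the sample size.

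**What to change.** Keep 102 and correct the last sentence of section 2.7.1, for example: *With 51 participants per group, 42 remain evaluable if the loss is no more than 17.6%; at a 20% loss (about 41 per group) power is about 79% by the same formula.* This costs one sentence and a slightly less favourable statement of the tolerated loss or the power. It needs no further participants and changes neither the design nor the analysis.

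If the sponsor prefers to hold both the 20% loss and the 80% power, the text should state 53 per group and 106 in total, with the abstract and section 2.2 changed to match. That costs 4 more participants.

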#### Statistical analysis

2.7.2

The statistical analyses will be performed using the SPSS 20.0 statistical software. Continuous data will be represented by the mean, standard deviation, median, minimum value, and maximum value. Categorical data will be represented by percentage. For the data with normal distribution, the *t* test or rank-sum test will be used for continuous data, and a nonparametric test or *χ*^2^ test for categorical data. A rank-sum test or *χ*^2^ test will be used to analyze the difference between 2 independent samples. Statistical analyses will be 2-sided tests. A *P* value <.05 will be considered statistically significant.

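### The test rules in the statistical analysis section are misstated and contradict each other; one named test is needed for the binary primary outcome and one stated method for the continuous changes

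*Protocol article*

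**What the plan says.** Protocol article, section 2.7.2 (Statistical analysis), gives the test rule in two consecutive sentences.

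- The first is introduced by "For the data with normal distribution". Under that condition it says that a t "test or rank-sum test will be used for continuous data, and a nonparametric test or" chi-square will be used for categorical data.
- The second covers comparisons between two independent samples and lists only rank-sum or chi-square.

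No criterion for choosing within either pair is given, and no test is tied to the primary outcome. All tests are two-sided, and a P "value <.05 will be considered statistically significant".

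Section 2.6.1 makes the primary outcome a responder percentage, so it is binary. Section 2.6.2 lists the continuous outcomes (changes in CSBMs, SBMs, difficulty score and PAC-QOL total), all of them secondary. Section 2.7.1 sizes the trial on the primary: the responder rate "may be 70% in the EA group and 40% in the TENS group", and "each group size should be 42, with an alpha risk of 5% and a beta risk of 20"%. It then adds an allowance for losses: "Assuming a 20% expulsion rate, a total of 102 participants (51 participants in each group) will be required".

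**The concern.** This is faulty text rather than detail left to a later document. An analysis plan written from section 2.7.2 could not follow it and would have to overrule it. There are four faults:

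1. The normality condition governs the rank-sum test as well as the t test, so it does not separate them.
2. It also governs the categorical tests, where normality has no meaning.
3. Data that are not normal have no rule.
4. The trial has two parallel arms, so the two-sample sentence covers every between-group comparison, and it excludes the t test that the previous sentence allows.

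The primary outcome is left with an open choice between an unspecified nonparametric test and a chi-square test that is not said to be corrected or uncorrected. Participants and acupuncturists are not blinded and the outcome comes from a diary. A test fixed in advance is therefore an inexpensive safeguard that the sponsor fully controls. What has to be established is how far the open choice can move the primary result.

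**Working it through.** **Inputs (section 2.7.1).** Rates 70% (EA) and 40% (TENS); two-sided alpha 5%; power 80%; 42 evaluable per group; 51 per group randomised.

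**Step 1: reproduce the 42.** Pooled-variance formula without continuity correction, with mean rate p̄ = (0.70 + 0.40)/2 = 0.55:

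n = [1.960·√(2·0.55·0.45) + 0.842·√(0.70·0.30 + 0.40·0.60)]² / 0.30²

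= (1.379 + 0.565)² / 0.09 = 41.97, rounded up to **42**.

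The stated figure is reproduced. The unpooled variant gives 39.2, so 40; the continuity-corrected variant gives 48.4, so 49. The plan's 42 therefore corresponds to the uncorrected Pearson chi-square test. With the loss allowance, 42 × 1.2 = 50.4, rounded up to 51, also as stated.

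**Step 2: the candidate tests on a binary outcome.** With tie correction, the rank-sum statistic on 0/1 data equals Pearson's chi-square × (N − 1)/N. At N = 84 the factor is 83/84 = 0.988; at N = 102 it is 101/102 = 0.990. The two are nearly the same test. Fisher's exact test and the continuity-corrected chi-square are clearly more conservative.

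Borderline tables (P values):

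| Responders | Pearson | Rank-sum | Corrected chi-square | Fisher |
|---|---|---|---|---|
| 29/42 vs 20/42 | .046 | .048 | .077 | .076 |
| 25/42 vs 16/42 | .0495 | .0508 | .081 | .080 |
| 30/51 vs 20/51 | .048 | .049 | .075 | .074 |

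**Step 3: exact enumeration.** For each n, every possible 2×2 table was tested at P < .05 and weighted by its binomial probability.

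Power at 70% versus 40%:

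| n per group | Pearson | Rank-sum | Corrected chi-square or Fisher |
|---|---|---|---|
| 42 | 82.8% | 80.0% | 76.4% |
| 51 | 88.6% | 88.6% | 84.2% |

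Probability that the verdict differs from Pearson's:

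| n per group | True rates | Rank-sum | Fisher |
|---|---|---|---|
| 42 | 70% vs 40% | 2.7% | 6.4% |
| 42 | 60% vs 40% | 5.5% | 8.8% |
| 51 | 70% vs 40% | 0% | 4.4% |
| 51 | 60% vs 40% | 0% | 8.0% |

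The 60% versus 40% row is an assumption of this review, chosen to show a smaller effect than planned.

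**Step 4: type I error.** With both rates at 50% (also assumed), the exact rejection rate at 42 per group is 6.3% (Pearson), 4.7% (rank-sum) and 3.8% (Fisher). At 51 per group it is 5.9%, 5.9% and 3.7%.

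**The case against.** The best defence is that section 2.7.2 names neither Fisher's test nor a continuity correction. The only nonparametric test it names is rank-sum, and its two-sample sentence offers only rank-sum or chi-square. Between those two the primary hardly moves: 29/42 versus 20/42 is significant by both, no table changes verdict at 51 per group, and both keep at least 80% power at 42. This stands, and it limits the point. What it does not settle is that the sentence on categorical data says only that the test is nonparametric, and that chi-square is not described as corrected or uncorrected. The more conservative readings are therefore open, though not stated.

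Three stronger readings might be inferred, and the document does not support them:

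- *That the choice of t or rank-sum can decide the primary.* It cannot. The primary is binary and the continuous outcomes are all secondary.
- *That 42 per group is wrong because a corrected formula needs 49.* The 42 is correct for the uncorrected chi-square. It would fall short only for a test that the article does not name.
- *That the single .05 threshold inflates error through the many secondary comparisons.* There is one primary outcome and one two-arm comparison, so secondary tests leave the primary's alpha untouched. Handling of secondary multiplicity is commonly left to an analysis plan, which is not shown here.

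**Conclusion.** The point holds as a defect of wording with a limited effect. The two sentences in section 2.7.2 are wrong as written and inconsistent with each other, whatever a separate analysis plan may say.

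For the primary outcome, the size depends on what the nonparametric option means. Read as rank-sum, the effect is negligible: 0% of verdicts differ at 51 per group and 2.7% at 42, under the planned rates. Read to include Fisher's test or a continuity correction, about 4% to 9% of verdicts differ at 70% or 60% versus 40%. Power at 42 per group is then 76% against the stated 80%; at 51 per group it is 84%, so the shortfall arises only if losses reach the planned allowance. In either case only results near the threshold are affected.

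For the continuous secondary outcomes the contradiction is complete, because the document both allows and excludes the t test. These figures assume independent binomial responses, equal groups and the rates shown.

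**What to change.** Rewrite the two sentences in section 2.7.2 so that they:

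1. Name the Pearson chi-square test without continuity correction for the primary outcome, as the test that reproduces the 42 per group, and report the risk difference with a 95% CI.
2. Remove the normality condition for categorical data.
3. Replace the contradictory choice between t and rank-sum with one prespecified baseline-adjusted model for the continuous change outcomes, with rank-sum as a sensitivity analysis.

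The cost is wording only; the 42 and 51 per group and the total of 102 stay as they are. One consequence should be accepted knowingly: the uncorrected test can run slightly above its nominal level (5.9% at 51 per group and 6.3% at 42, if both rates are 50%). If the sponsor prefers a conservative test, it should name that test in advance and state its power, 76% at 42 evaluable per group.

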### Study setting and recruitment

2.2

This study will be conducted from July 2018 to December 2020 in Guang’anmen Hospital, China Academy of Chinese Medical Sciences. A total of 102 participants with functional constipation will be recruited openly through posters, hospital websites, and networks. A postgraduate is responsible for consultation with the participants and screening, filling out the screening form, recording demographic data, history of diagnosis and treatment, inclusion and exclusion criteria, and other basic data of the participants. The qualified participants will undergo a baseline evaluation for 1 week.

For inclusion in this study, participants will conform to the following criteria: with functional constipation as defined by the Rome III criteria;^[13]^ specific symptoms including laborious defecation or <3 times per week, hard stool, a sense of obstruction, needing an auxiliary defecation method; aged 18 to 75 years; volunteered to participate and provided signed informed consent.

Potential participants with any of the following will be excluded from this study: irritable bowel syndrome; organic constipation or secondary constipation caused by endocrine, metabolic, neurogenic, or postoperative diseases; combined with severe heart, liver, or kidney damage; cognitive impairment, aphasia, or mental disorders; inability to cooperate with the examination or treatment; pregnant or lactating; abdominal aortic aneurysm; abnormal enlargement of the liver or spleen; blood coagulation dysfunction or chronic use of anticoagulants such as Warfarin and Heparin; or with an installed cardiac pacemaker.

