#### Secondary outcomes

2.6.2

The secondary outcome measures are the following 7 items: percentage of participants with an average increase from baseline of at least 1 CSBM at weeks 4, 20, and 32; change in the number of CSBMs at weeks 4, 8, 20, and 32; change in the number of spontaneous bowel movements (SBMs) at weeks 4, 8, 20, and 32; percentage of participants with type 3 or type 4 stool at weeks 4, 8, 20, and 32, as defined by the Bristol scale;^[17]^ change in average score for difficult defecation at weeks 4, 8, 20, and 32; change in total score on the PAC-QOL questionnaire ^[18]^ at the end of week 8, relative to baseline; and the percentage of participants using cathartics, and the average amount of cathartics, at weeks −1, 4, 8, 20, and 32.

The participants will be asked to record a diary of defecation every day during weeks −1, 4, 8, 20, and 32 after randomization. The recordings are to include bowel movements, SBMs, CSBMs, the stool character, degree of difficulty in defecation, and the use of auxiliary defecation methods. All adverse events that occur during the trial will be recorded. Serious adverse events should be reported to the principal investigator immediately.

The participants’ expectations will be assessed before the intervention with 4 brief questions for which the answers chosen may be “Yes,” “No,” or “Unclear,” as follows: “Do you think EA is effective for treating illness?”; “Do you think EA will help improve your symptoms?”; “Do you think TENS is effective for treating illness?”; “Do you think TENS will help improve your symptoms?”. In addition, a fifth question (“Which kind of treatment do you prefer?”) may be answered as “EA,” “TENS,” or “Does not matter.”

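### The continuous change outcomes are to be compared by unadjusted two-sample tests, so baseline values already collected are not used to gain precision

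*Protocol article*

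**What the plan says.** Secondary outcomes (2.6.2) defines four continuous outcomes as change:

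- CSBMs: "change in the number of CSBMs at weeks 4, 8, 20, and 32".
- SBMs: "change in the number of spontaneous bowel movements (SBMs) at weeks 4, 8, 20, and 32".
- Difficulty of defecation: "change in average score for difficult defecation at weeks 4, 8, 20, and 32".
- PAC-QOL total score: change "at the end of week 8, relative to baseline".

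The baseline for each is already part of the trial. Under Study setting and recruitment (2.2), "The qualified participants will undergo a baseline evaluation for 1 week". Section 2.6.2 has participants "record a diary of defecation every day during weeks −1, 4, 8, 20, and 32 after randomization", so week −1 supplies the diary baselines. The PAC-QOL change itself requires a baseline score.

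Statistical analysis (2.7.2) has a t "test or rank-sum test will be used for continuous data", and a rank-sum or chi-square "test will be used to analyze the difference between 2 independent samples". The article names no covariate, regression or other adjusted model.

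**The concern.** A raw change score fixes the coefficient on baseline at 1. The data usually support a different coefficient, namely the regression slope of follow-up on baseline. Where the slope is below 1 the change score over-corrects for baseline, and where it is above 1 it under-corrects. Either way two things follow: the estimate is less precise than it could be, and part of any chance baseline difference between the arms passes into the observed treatment difference.

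The trial is sized for a single binary comparison. All continuous results, including the week 20 and week 32 changes, must come from the same 102 participants, and the diary baseline is a single week. An avoidable loss of precision is worth removing when the data for the remedy are already in hand. A rank-sum test of change, which is one literal reading of 2.7.2, also yields no mean difference with a confidence interval.

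**Working it through.** **1. The plan's own figure.** Sample size (2.7.1) assumes 70% against 40%, two-sided alpha 5% and power 80%. With the pooled variance formula and mean proportion 0.55:

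n = [1.96·√(2·0.55·0.45) + 0.8416·√(0.7·0.3 + 0.4·0.6)]² / 0.30² = 41.97, so 42 per group.

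This matches the article. It concerns the binary primary outcome only, and nothing below alters it.

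**2. Variance formulas.** Let s0 and s1 be the baseline and follow-up SDs, k = s1/s0, and r the baseline to follow-up correlation. Per participant:

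- Raw change: s0² + s1² − 2·r·s0·s1
- ANCOVA (large sample): s1²·(1 − r²)
- Difference: (s0 − r·s1)², which is never negative
- Ratio, ANCOVA to change: k²(1 − r²) / (k² + 1 − 2rk)

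The difference is zero exactly when the slope r·k equals 1. Apart from one degree of freedom, ANCOVA does not lose to the raw change. At k = 1 the ratio reduces to (1 + r)/2.

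**3. Numbers.** The article gives neither r nor k, so both are assumptions. The power column takes 42 per group and an effect for which the raw-change test has 80% power: Φ((1.96 + 0.8416)/√ratio − 1.96).

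| k | r | slope r·k | variance ratio | CI width factor | power with ANCOVA |
|---|---|---|---|---|---|
| 1 | 0.3 | 0.30 | 0.91/1.40 = 0.65 | 0.81 | 93.5% |
| 1 | 0.5 | 0.50 | 0.75/1.00 = 0.75 | 0.87 | 89.9% |
| 1 | 0.7 | 0.70 | 0.51/0.60 = 0.85 | 0.92 | 86.0% |
| 1.5 | 0.3 | 0.45 | 2.0475/2.35 = 0.87 | 0.93 | 85.1% |
| 1.5 | 0.5 | 0.75 | 1.6875/1.75 = 0.96 | 0.98 | 81.4% |
| 1.5 | 0.7 | 1.05 | 1.1475/1.15 = 1.00 | 1.00 | 80.1% |
| 2 | 0.5 | 1.00 | 3.00/3.00 = 1.00 | 1.00 | 80.0% |

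At k = 1, ANCOVA needs 42·0.65, 42·0.75 and 42·0.85, rounded up to 28, 32 and 36 per group, to match the raw-change test at 42. At k = 1.5 the figures are 37, 41 and 42.

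**4. Why the gain is probably smaller for counts.** CSBMs and SBMs are weekly counts that are expected to rise, and the variance of a count usually rises with its mean, which puts k above 1. As an illustration with assumed values, take a gamma-Poisson model with baseline mean 1 per week, follow-up mean 2, shape 4 and a proportional gain. The baseline variance is 1 + 1/4 = 1.25, the follow-up variance 2 + 4/4 = 3 and the covariance 2/4 = 0.5. Then k = √(3/1.25) = 1.55, and the ratio is (3 − 0.25/1.25)/(1.25 + 3 − 1) = 2.8/3.25 = 0.86. With shape 1 the variances are 2 and 6 and the covariance is 2, so the slope is 1 and the ratio is 1.00. A gain of the same size for everyone would keep k closer to 1 and the benefit larger. The documents do not settle which applies.

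**5. Chance imbalance.** The standard error of the baseline mean difference is √(2/51) = 0.20 SD at 51 per group and √(2/42) = 0.22 SD at 42. A baseline difference of d moves the raw-change result by (r·k − 1)·d relative to the adjusted one. With d = 0.20 SD and slope 0.5, that is 0.10 baseline SD in size.

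**The case against.** The case against has several strong parts.

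- **Validity.** A reader might infer that the planned comparison is biased or its type I error inflated. The documents do not support that. Allocation is randomized, so the unadjusted comparison is unbiased over repeated trials and its standard error already allows for chance imbalance. What remains is that a given observed result depends on the imbalance that happened to arise.
- **Size.** A reader might infer a guaranteed loss whenever r is below 1, or take the k = 1 rows as the whole range. Neither holds. The condition is a slope r·k different from 1, and the k = 1 rows assume equal spread before and after treatment, which fits rising counts poorly. At k = 1.5 the gain is 13% of the variance or less for these r. This objection stands, and the range must extend to almost no gain.
- **Reach.** A reader might extend the point to the main conclusion. The primary outcome is a responder percentage, its 42 per group is unaffected, and only secondary outcomes are at issue.
- **Condensed text.** Section 2.7.2 is one generic paragraph that ties no test to any outcome, and an unseen analysis plan could specify adjustment. That comparison of raw changes follows is therefore an inference. It is a fair one: the article is not silent on method, it names its between-group tests, and all of them are unadjusted. By contrast, the lack of any mention of stratification under Randomization (2.3) is mere silence, and nothing here relies on it.

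**Conclusion.** The point holds as an improvement in efficiency for secondary outcomes, not as an error of validity. As written, 2.7.2 compares four continuous change outcomes without using their baselines as covariates. Depending on the assumed r (0.3 to 0.7) and k (1 to 1.5), adjustment lowers the variance by anything from about 35% to almost nothing. The smaller gains are more likely for CSBMs and SBMs. A k nearer 1, and so a larger gain, is plausible for the difficulty score and PAC-QOL, but the documents do not say. In large samples adjustment does not lose precision beyond one degree of freedom, so the uncertainty about r and k is no reason to leave it out.

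**What to change.** In 2.7.2, replace the two-sample tests for these four outcomes by ANCOVA with treatment and the outcome's own baseline value as covariate, using robust standard errors for the skewed counts. For the outcomes measured at weeks 4, 8, 20 and 32, a repeated-measures model with baseline and treatment-by-week terms serves equally well. Report the adjusted mean difference with its 95% CI. Leave the analysis of the binary primary outcome as it is.

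The wording should be fixed before any data are seen by group, so that the choice to adjust cannot follow the results. The cost is a change of text and a little analyst time. Data collection and sample size stay the same, and the named software fits ANCOVA.
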